### Quality-adjusted life years

We will estimate QALYs using the EQ-5D-5L tariff that is recommended by NICE at the time of the analysis; this is currently the van Hout “cross-walk” tariff [39]. We will estimate QALYs using linear interpolation between time points. We will undertake exploratory analysis to assess the QALY loss related to urodynamics (e.g. anxiety and discomfort) by estimating the degree to which EQ-5D-5L values at 3 months post-randomisation are affected by time since urodynamic testing. If a robust estimate of QALY loss is produced, we will examine the impact of its incorporation into the cost-effectiveness analysis using a sensitivity analysis.

### Within trial cost-effectiveness analysis

The within trial analysis will follow the best practice guidelines [40]. The analysis will calculate total costs and QALYs for each patient and estimate the incremental costs and QALYs using a seemingly unrelated regression model with baseline covariates including age and baseline EQ-5D-5L score and missing data imputed using multiple imputation [41, 42].

We will base the cost-effectiveness acceptability curves on the adjusted and imputed analysis described above. We will undertake deterministic sensitivity analyses to look at three sources of methodological uncertainty; societal perspective, the EQ-5D-5L tariff and any QALY loss associated with urodynamics identified in the exploratory analysis described above. Undertaking a sensitivity analysis with the EQ-5D-5L tariff is required as alternative tariffs are available; the current recommended tariff is the van Hout “cross-walk” tariff [43]

### Patient lifetime cost-effectiveness analysis

The primary analysis is model based. Such an approach is considered superior to trial-based analyses as it can be designed to better fit the research question and incorporate other relevant sources of data [44]. In this particular situation, the model can incorporate the longer-term costs and consequence of using urodynamics which cannot be observed in the trial. However, the first 15 months of the model will be based on the trial results. The structure of the model beyond 15 months will be based on a pre-existing model [18]. A key improvement over this model is the use of more appropriate utilities taken from the trial. In addition, we will undertake targeted literature searches to assess whether any relevant new studies have been published for the other parameters.

In line with the Rachaneni model [18], exploratory analyses examine whether targeted urodynamics for a subgroup of patients has the potential to be cost-effective. In addition to Rachaneni, we will undertake two exploratory analyses:
A non-randomised comparison of the cost-effectiveness of different sequence of treatments (i.e. initiated on BoNT-A vs SNM).A non-randomised comparison of the cost-effectiveness of SNM according to clinical assessment only compared to treatment guided by urodynamics.

These two comparisons take account of the lack of randomisation using methods consistent with those of the analogous clinical analyses.

We will also undertake a probabilistic sensitivity analysis on the modelled results and its associated incremental cost-effectiveness ratio, cost-effectiveness plane and cost-effectiveness acceptability curves generated. We will undertake a value of information analysis using SAVI (http://savi.shef.ac.uk/SAVI/). The partial values are used to identify those parameters where there is greatest value in resolving outstanding uncertainty. We will undertake a deterministic sensitivity analyses to look at the three sources of methodological uncertainty; societal perspective, the EQ-5D-5L tariff and the length of disutility associated with urodynamics.

### Qualitative interviews

A standardised approach will be employed in accordance with published qualitative research methods [45–49].

Interviews are semi-structured and follow a topic guide informed by literature review and discussion between study researchers and encourage participants to discuss their perspectives with regard to the qualitative study aims. Interviews are audio recorded, transcribed verbatim (including descriptions of non-verbal factors where appropriate) and uploaded onto a qualitative software package (QSR Nvivo 10) to aid data management. The qualitative researcher will conduct the analyses according to principles of thematic content analysis.

We will use theoretical purposive (non-probability) sampling to ensure the diverse characteristics of the population are sampled (e.g. participants varying in age, relevant clinical history (MUI vs OAB), investigations received (urodynamics and comprehensive clinical assessment versus comprehensive clinical assessment only), and treatments received (SNM vs. BoNT to include day case vs. local anaesthetic procedures). Sampling and analyses continue in iterative cycles until data saturation is achieved. It is anticipated a minimum of thirty to forty patient interviews will be undertaken to effectively capture the opinions of those in both arms of randomisation, the numerous potential treatments and treatment considered successful and failed. Approximately ten to fifteen clinician interviews are proposed to explore the clinical aspects of urodynamics with regard to clinical decision-making.

### Interim analyses {21b}

There will be no interim analyses.

### Methods for additional analyses (e.g. subgroup analyses) {20b}

We will perform a secondary supporting analysis of the primary outcome using ordinal logistic regression on the 7-point PGI-I scale. This will use a generalised ordered logit model with the partial proportional odds model (for example, as implemented in “gologit2” in Stata) to relax this restrictive assumption of the full proportional odds model. We will also include a suitably defined per protocol analysis as a secondary supporting analysis.

We will compare the outcomes in pre-specified subgroups of participants with OAB vs MUI. In addition, we will explore, in a non-randomised analysis, the following:
Clinical and cost-effectiveness of the different treatment pathways of those initiated on BoNT-A treatment vs those initiated on SNM treatment.Clinical and cost-effectiveness of SNM treatment according to clinical assessment only compared to treatment guided by urodynamics.Clinical and cost-effectiveness of BoNT-A treatment according to clinical assessment only compared to treatment guided by urodynamics

### Methods in analysis to handle protocol non-adherence and any statistical methods to handle missing data {20c}

Analysis will be by intention-to-treat. We will assess how robust all findings are to any missing data (anticipated to be no more than 10% for the primary outcome) using multiple imputation approaches under an assumption of missing at random. We will consider non-ignorable missing data mechanisms if the patterns of missing data across the two randomised groups suggest this is appropriate.

### Plans to give access to the full protocol, participant-level data and statistical code {31c}

The full protocol is available on the funder’s website (https://www.journalslibrary.nihr.ac.uk/programmes/hta/1515005/#/). Non-identifiable participant-level data may be available on request to the Chief Investigator (CI), [name] ([contact])

## Oversight and monitoring

### Composition of the coordinating centre and trial steering committee {5d}

The Trial Office is in CHaRT based within the Health Services Research Unit, University of Aberdeen and provides day to day support for the clinical centres. The Trial Manager takes responsibility for the day to day transaction of trial activities, for example approvals, site set-up and training, oversight of recruitment and follow-up rates. The Data Coordinator provides clerical support to the trial, including organising all aspects of the questionnaires (mailing, tracking and entering returned data using the trial web data entry portal).

The FUTURE Trial Office Team (CI, trial manager, data coordinator, statistician) meets formally, approximately fortnightly during the course of the study to ensure smooth running and trouble-shooting, but more frequently during the set-up phase as required.

The trial is supervised by its Project Management Group (PMG). The group consists of grant holders (clinicians, statisticians, health economists and qualitative researchers) and representatives from the Trial Office. Observers are invited to attend at the discretion of the PMG. The PMG meets approximately every 2 months in the first and last 6 months of the trial and approximately every 3 months in-between.

The PMG has the expertise to cover the clinical, methodological and management aspects of the FUTURE study.

Any modification to the project is normally discussed by the PMG, and when relevant by the Trial Steering Committee (TSC) and is approved by the Sponsors and funder before application to the Research Ethics Committee (REC) and Research and Development (R&D). An exception to the above is in the case where an immediate implementation of safety measures is required; the Sponsor is then notified as soon as possible.

A TSC oversees the conduct and progress of the FUTURE study. The TSC meets annually and includes an independent chair, clinical and methodological expertise and a lay representative.

### Composition of the data monitoring committee, its role and reporting structure {21a}

An independent Data Monitoring Committee (DMC) oversees the safety of participants in the FUTURE study. The DMC Charter documents the terms of reference of the DMC and the names and contact details. This is filed in the Trial Master File. The committee meets every 6 to 12 months to monitor the study data and make recommendations as to any modifications that are required to be made to the protocol or the termination of all or part of the study. The study has adopted the DAMOCLES Charter for DMCs [50].

### Adverse event reporting and harms {22}

In FUTURE, we will only record adverse events (AEs) and serious adverse events (SAEs) related to the study interventions. A serious adverse event is defined as any AE that results in death, is life threatening (i.e. the subject was at risk of death at the time of the event; it does not refer to an event which hypothetically might have caused death if it were more severe), results in persistent or significant disability or incapacity, requires hospitalisation or prolongation of existing hospitalisation or is otherwise considered medically significant by the investigator.

All AEs and SAEs meeting the criteria for recording within the trial are recorded from the time a participant consents to join the trial until the end of their follow-up period. Every follow-up visit and questionnaire will inquire on expected AEs/SAEs. In addition, we will use open ended and non-leading verbal questioning of the participant to enquire about AE/SAE occurrence or re-admission to hospital and any further treatment received.

Depending on severity, when an AE/SAE meeting the criteria for recording within the FUTURE Study occurs, it is the responsibility of the local PI (or delegate) to review appropriate documentation (e.g. hospital notes, laboratory and diagnostic reports) related to the event. The PI or delegate should then record all relevant information in the CRF (and on the SAE form if required).

PI or delegates are responsible for notifying the trial office of any SAEs that require to be recorded in line with the FUTURE study protocol. If an SAE is recorded on a participant questionnaire, the Trial office liaises with the relevant study site to obtain further information.

When an SAE form is uploaded onto the trial website, the Trial Manager is automatically notified. If, in the opinion of the local PI and/or the CI, the event is confirmed as being *serious* and *related* and *unexpected*, the CI or Trial Manager notifies the sponsor within 24 h of receiving the signed SAE notification. The sponsor provides an assessment of the SAE. A Sponsor cannot downgrade an assessment from the PI or CI. Any disparity is resolved by further discussion between these parties.

The CI or delegate reports any related and unexpected SAEs to the REC within 15 days of the CI becoming aware of it.

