## Trial design {8}

This is a pragmatic, multi-centre, superiority RCT comparing the effectiveness and cost-effectiveness of routine urodynamics investigation and comprehensive clinical assessment versus comprehensive clinical assessment only in the management of women with refractory OAB symptoms (Fig. 1). An internal pilot study with stop/go criteria is embedded within the RCT to establish whether the projected recruitment rate is achievable.

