### Treatment pathways following intervention

In the urodynamics plus comprehensive clinical assessment arm the treatment pathway is guided by the urodynamics diagnosis and is in line with the NICE guideline (CG171; See Additional file 1 Treatment Pathway A). The latter recommends BoNT-A 200 units as the first treatment; however since its publication, further evidence confirmed the efficacy of BoNT-A treatment at the lower dose of 100 units with less adverse events [35] and it has since been licensed in that dose. Note: Subsequent NG123 also recommended initial treatment with 100 units [13].

NICE CG171 also recommends offering SNM treatment for patients who are unable or unwilling to perform CISC or following unsuccessful BoNT-A treatment pending MDT discussion [11]. However, in view of the lack of robust evidence on the best sequence of treatments in women with refractory OAB, participants in both arms of the FUTURE study can be offered either BoNT-A (100 units) or the SNM test; the decision will be discussed in the local MDT or as per local standard best practice. This approach will vary between units depending on their local clinical practice and the availability of treatments. Participants with other diagnoses on urodynamics would be offered the appropriate treatments.

Depending on the clinical outcome of treatment, we will offer participants with persistent or de novo symptoms urodynamic tests and treatment accordingly or further/ repeat treatment according to comprehensive clinical assessment only.

In the comprehensive clinical assessment only arm, the treatment pathway is guided by the clinical diagnosis and non-invasive tests (See Additional file 1 Treatment Pathways B). Considering the evidence above, we will offer participants with clinically diagnosed refractory OAB or urgency predominant MUI either BoNT-A (100 units) or SNM test. We will discuss the decision in the local MDT or as per local standard best practice. This approach will vary between units depending on their local clinical practice and the availability of treatments. We will offer participants with other clinical diagnoses (such as overflow incontinence or SUI predominant MUI) and other appropriate treatments such as CISC, SUI surgery or other medical/conservative treatments as per local standard best practice.

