### Outcomes {12}

The primary outcome measure is participant-reported success at 15 months post-randomisation (approximately 12 months post-treatment) as measured by the PGI-I.

The PGI-I is a validated single item questionnaire designed to assess the participant’s impression of changes in her urinary symptoms. The PGI-I asks the participant to best describe her urinary symptoms, compared with how they were before the study intervention, on a 7-point scale scored as: (1) “very much improved,” (2) “much improved,” (3) “improved,” (4) “same,” (5) “worse,” (6) “much worse,” or (7) “very much worse. “Success” is defined as responses of “very much improved” or “much improved”; this will capture whether the women are satisfied with their treatment.

The primary economic outcome is the incremental cost per QALY gained of urodynamics and comprehensive clinical assessment compared to comprehensive clinical assessment only, modelled over the lifetime of the patients.

Secondary outcome measures are as follows:
○ A less strict definition of success at 15 months derived from the PGI-I where success is defined as a response of “very much improved”, “much improved”, or “improved”.○ Proportion of women receiving invasive treatment at 6 and 15 months post-randomisation.○ Participant-reported outcomes at 3, 6 and 15 months post-randomisation including:▪ OAB symptoms measured by the International Consultation on Incontinence Questionnaire Overactive Bladder (ICIQ-OAB) and the Urgency Perception Scale (UPS);▪ Urgency and UUI episodes measured using the bladder diary;▪ Other urinary symptoms measured using the 3 domains of the International Consultation on Incontinence Questionnaire Female Lower Urinary Tract Symptoms (ICIQ-FLUTS; filling, voiding and incontinence) and the bladder diary;▪ Generic health-related QoL status measured using general (EQ-5D-5L) and condition specific (International Consultation on Incontinence Questionnaire Lower Urinary Tract Symptoms Quality of Life; ICIQ-LUTSqol) QoL assessment tools.○ Adverse events:▪ All serious adverse events;▪ UTI requiring antibiotic treatment;▪ For subsequent treatments:

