○ BoNT-A treatment: urinary retention requiring clinical intervention (e.g. catheterisation); CISC.○ SNM: infection of the SNM lead; lead migration, revision of surgery; wound infection.○ SUI surgery: Bladder injury; intra operative bleeding requiring return to theatre; post-operative wound infection; nerve injury; tape exposure/extrusion into vagina/lower urinary tract; tape excision/division; tape infection; new onset and related pelvic pain; urinary retention requiring intervention (e.g. catheterisation); CISC; others.○ Qualitative study outcomes:▪ Participants’ attitudes to invasive testing and expected outcomes (prior to randomisation or knowing their allocated study group);▪ Participants’ attitudes to potential treatment options (prior to randomisation or knowing their allocated study group);▪ Participants’ experience of urodynamics and opinions regarding treatment outcome to include evaluation of treatment satisfaction or desire for further treatment (3 to 6 months post-treatment);▪ Surgeon attitudes to the influence of urodynamics on decision-making (at start of the study and 6 to12 months after starting recruitment at their sites).○ Secondary economic outcomes include:▪ Incremental cost per QALY gained of urodynamics and comprehensive clinical assessment compared to comprehensive clinical assessment only up to 15 months;▪ Incremental cost per QALY gained of BoNT-A vs SNM as the initial treatment for refractory OAB over the lifetime of patients;▪ Incremental cost per QALY gained of SNM test and BoNT-A treatment according to clinical assessment only compared to treatment guided by urodynamics over the lifetime of patients;▪ Expected value of perfect information and associated partial values over the lifetime of patients.

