## Assignment of interventions: Blinding

### Who will be blinded {17a}

Participants, clinical staff or the central trial team cannot be blinded to the allocated procedure because of the nature of the interventions.

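### The adverse event section limits recording to intervention-related events, so the declared outcome of all serious adverse events cannot be produced, and unblinded attribution could distort the harms comparison

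*Protocol article*

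**What the plan says.** Adverse event reporting and harms {22} sets the recording rule: "In FUTURE, we will only record adverse events (AEs) and serious adverse events (SAEs) related to the study interventions". The recording window runs from consent to the end of follow-up, but only for events that meet this rule. The local PI or a delegate reviews the source documents and records the event. Expected events are asked about at every visit and in every questionnaire, with neutral open questions added.

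Outcomes {12} lists the harms among the secondary outcomes. They include "All serious adverse events" and "UTI requiring antibiotic treatment", neither qualified by relatedness. Events tied to subsequent treatments follow, for example "BoNT-A treatment: urinary retention requiring clinical intervention (e.g. catheterisation); CISC", with similar lists for SNM and SUI surgery.

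Trial design {8} describes the trial as "comparing the effectiveness and cost-effectiveness of routine urodynamics investigation and comprehensive clinical assessment versus comprehensive clinical assessment only". Treatment comes under a later heading, "Treatment pathways following intervention". On blinding, section {17a} says: "Participants, clinical staff or the central trial team cannot be blinded to the allocated procedure".

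**The concern.** The two sections cannot both be followed. One names an outcome that includes every serious adverse event; the other tells sites to record only those that are related. An analysis plan cannot recover events that sites were told not to record.

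The rule also makes a judgement of cause the condition for an event to exist in the dataset. In an open trial that judgement is made by people who know the allocation, and the Rationale for the trial names UTI as a known risk of urodynamics. Staff therefore have a documented reason to attribute a UTI to the test in one arm. If attribution differs by arm, the comparison of recorded events mixes incidence with attribution. That matters here because the harm of an invasive test is part of deciding whether the test is worthwhile.

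**Working it through.** **Step 1: set the recording rule against each listed outcome.** Section {22} does not define study interventions. Two readings are possible.

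- *Narrow:* the two assessment strategies only. Trial design {8} and Intervention description {11a} support this, as does the heading that places treatment after the intervention.
- *Broad:* assessment plus the treatments that follow. Table 1 supports this with a row for interventions received at 3, 6 and 15 months, and the background section also calls BoNT-A and SNM interventions.

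| Outcome in {12} | Recordable, narrow reading | Recordable, broad reading |
|---|---|---|
| All SAEs | Only those related to assessment | Only those related to assessment or treatment |
| UTI needing antibiotics | Only if related to assessment | Only if related to assessment or treatment |
| BoNT-A, SNM and SUI surgery complications | Excluded | Included |

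The SAE and UTI rows conflict with the rule on both readings. The last row conflicts on the narrow reading only.

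**Step 2: what selective recording can do.** The plan states no figure to reproduce and gives no SAE rate or attribution probability. What follows is an illustration under assumptions. Let both arms have the same true risk t, and let a and b be the probabilities that an event is judged related in the urodynamics and clinical-assessment arms.

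- Recorded risks: p1 = t × a and p2 = t × b.
- Recorded risk ratio: (t × a)/(t × b) = a/b, whatever t is.
- Chance of a significant result at the two-sided 5% level, with 548 per arm (Sample size {14}): Φ[(|p1 − p2| − 1.96 × SE0)/SE1], where SE0 uses the pooled proportion and SE1 the separate ones.

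Example with t = 5%, a = 0.5, b = 0.3:

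- p1 = 0.025 and p2 = 0.015; expected recorded events 548 × 0.025 = 13.7 and 548 × 0.015 = 8.2.
- SE0 = √(2 × 0.020 × 0.980/548) = 0.00846.
- SE1 = √((0.025 × 0.975 + 0.015 × 0.985)/548) = 0.00845.
- Φ[(0.010 − 0.01658)/0.00845] = Φ(−0.78) = 0.22.

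Range, with a fixed at 0.5:

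| b | Recorded RR | t = 3% | t = 5% | t = 10% |
|---|---|---|---|---|
| 0.5 | 1.00 | 5% | 5% | 5% |
| 0.4 | 1.25 | 6% | 8% | 12% |
| 0.3 | 1.67 | 15% | 22% | 39% |
| 0.2 | 2.50 | 31% | 47% | 77% |

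The last three columns give the chance of a significant difference when the true rates are equal. In the first row there is no distortion, only loss: at t = 5%, 548 × 0.05 = 27.4 events per arm shrink to 13.7. If attribution ran the other way (a = 0.3, b = 0.5), the recorded ratio would be 0.60, so the direction is not fixed either.

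**The case against.** The strongest reply is that the events are probably collected in practice. Table 1 takes adverse events from both CRFs and participant questionnaires at 3, 6 and 15 months in both arms, the questionnaires go back to the central trial office, and an SAE reported on one prompts contact with the site. Nothing says that a UTI reported on a questionnaire is deleted if judged unrelated. The article also condenses a longer protocol, where study interventions may be defined.

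Much of this stands. It removes two stronger readings that a reader might infer.

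- *That complications of BoNT-A, SNM and surgery are dropped and the control arm has almost nothing to count as related.* This needs the narrow reading. BoNT-A or the SNM test is offered in both arms, BoNT-A is given through a cystoscope, and urodynamics may follow later in the clinical-assessment arm. A worked UTI example built on an uninstrumented control arm would contradict the document.
- *That the harms comparison is biased.* The text shows a route to bias, not its occurrence, size or direction. What the DMC sees cannot be judged either, as its charter is not shown.

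The reply does not remove the conflict over SAEs. Asking about an event is not the same as recording it, and section {22} permits recording only of related events. A fuller definition would settle the treatment complications but would still exclude unrelated SAEs. If the forms do capture everything, section {22} misdescribes the trial and needs correcting for that reason.

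**Conclusion.** Wrong as written; should be fixed. On any reading of study interventions, following section {22} makes the declared outcome of all SAEs impossible to produce, and UTIs judged unrelated are also outside the rule. This rests on the text alone. Exclusion of later-treatment complications is conditional on the undefined term.

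Bias in the between-arm comparison is a possibility. It requires attribution to differ by arm, for which unblinded staff have opportunity and, for UTI, a documented reason. Its size cannot be derived from the documents: across the assumed values the recorded risk ratio runs from 1.00 to 2.50 with equal true rates. The harms are secondary outcomes, and the primary PGI-I analysis is untouched.

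**What to change.** Reconcile section {22} with Outcomes {12}. Record every SAE and every adverse event listed in {12}, in both arms, whatever the attribution, over the window already stated. Keep relatedness and expectedness as recorded classifications used for expedited reporting to the sponsor and REC. State that complications of BoNT-A, SNM and SUI surgery are in scope.

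Timing limits what a forward change can achieve. Trial status gives 1022 women randomised by 16 March 2020, and all of them had passed 15 months by 16 June 2021, before protocol version 10.0 of 1 July 2021. That is 1022/1096 = 93% of the target. A new rule applied only from then would make ascertainment uneven over the trial. If unrelated SAEs were not collected and cannot be, relabel the outcome as SAEs related to study interventions or subsequent treatments, and define study interventions.

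The cost is a change of wording and some extra entries, since CRFs and questionnaires already ask about adverse events at 3, 6 and 15 months. The downside is more unrelated SAEs to log.
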